### **4 INVESTIGATIONAL PLAN**

#### **4.1 Overview of Study Design and Dosing Regimen**

This study will be a multi-center, open-label, phase 2 study, enrolling subjects with newly diagnosed MM requiring systemic chemotherapy. All dosing schedule is based on 28-day cycles. Subjects will receive treatment until disease progression or unacceptable toxicity (whichever occurs first).

Enrolled subjects will initially receive lenalidomide at 25 mg per dose (see below if previously unable to tolerate 25 mg) on Days 1-21. Carfilzomib will be dosed at 20 mg/m^2 on Days 1 and 2 and 36mg/m^2 thereafter (Days 8,9,15, and16). Alternative escalation will be allowed on Cycle 1 if the treating

investigator considers it necessary as follows: 20 mg/m^2 on Days 1 and 2 escalated to 27 mg/m^2 on Days 8 and 9, and then to 36 mg/m^2 on Days 15 and 16. Daratumumab will be administered by subcutaneous injection, provided as a fixed-dosed of 1800 mg and 30,000 units hyaluronidase per 15 mL (120 mg and 2,000 units/mL) for all cycles. The injection will be given by manual push over 3 to 5 minutes in the abdominal SC tissues in left/right locations, alternating between individual doses. Dexamethasone will be dosed at 40 mg PO per week for subjects < 75 years and 20 mg PO per week for subjects ≥ 75 years during Cycles 1-4. Dose modifications will be mandated based on aggressive schedule of dose modification for toxicities as per specific guidelines. Otherwise, patients will continue at their best tolerated dose of lenalidomide on Days 1-21 and their best tolerated dose of carfilzomib on Days 1, 2, 8, 9, 15, 16 in Cycles 1-4 and Days 1, 2, 15, 16 in Cycles 5-8.

All subjects will have monthly clinic visits for disease assessments. Treatment will continue on protocol for up to 24 months or if carfilzomib, lenalidomide and daratumumab are permanently discontinued. If dexamethasone is discontinued due to toxicity, carfilzomib, lenalidomide and daratumumab may be continued if tolerated without dexamethasone. Toxicity will be graded using the National Cancer Institute Common Terminology Criteria for Adverse Events version 4. Patients who complete 24 cycles will then continue single-agent lenalidomide at best tolerated dose (up to 25 mg) in 28-day cycles. This regimen will continue until there is progression of the disease or the toxicities require discontinuation of the drug.

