### **6.2.2.1 Contraception**

Females of childbearing potential must:

- Avoid pregnancy for at least 4 weeks before beginning lenalidomide.
- Have 2 negative pregnancy tests prior to starting treatment, the first test within 10 to 14 days and the second test 24 hours before prescribing lenalidomide.
- Take pregnancy tests weekly for the first 28 days of treatment.
- Take pregnancy test every 28 days during treatment after the first month. For women of childbearing potential with irregular menstruation, pregnancy tests must be taken weekly for the first 28 days of treatment and every 14 days during treatment.
- Agree to abstain from heterosexual sexual intercourse or to use 2 methods of effective contraception beginning 4 weeks prior to initiating treatment with lenalidomide, during therapy, during dose interruptions and for 90 days following the last dose of drug (more frequent pregnancy tests may be conducted if required per local regulations). Carfilzomib is prohibited in breast-feeding women.
- Abstain from donating eggs during the study and for 90 days after last dose of study drug.

A FCBP is defined as a sexually mature female who: 1) has not undergone a hysterectomy or bilateral oophorectomy, or 2) has not been naturally postmenopausal for at least 24 consecutive months (i.e., no menses at any time in the preceding 24 consecutive months). Amenorrhea following cancer therapy does not rule out childbearing potential.

Male subjects and their partners must use 1 highly effective method of birth control plus 1 additional effective method of birth control (contraception) at the **SAME TIME** during treatment and for 90 days following the last dose of drug, even if they have undergone a successful vasectomy. Male subjects must not donate sperm during the study and for 90 days after your last dose of study drug.

Highly effective methods of contraception include:

- Intrauterine device (IUD)
- Hormonal therapy (birth control pills, injections, implants)
- Tubal ligation
- Vasectomy

Additional effective methods include:

- Latex condom
- Diaphragm
- Cervical Cap

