## **8.2 Adverse Event Reporting Procedures**

Information about all AEs, whether volunteered by the subject, discovered by the treating investigator questioning, or detected through physical examination, laboratory tests or other means, will be collected and recorded in eVelos and followed as appropriate.

All adverse events **must** be reported in routine study data submissions to the Lead PI who will review and will be responsible for alerting all participating sites about the AE as required. **AEs reported using the Serious Event Reporting Form and/or MedWatch Form discussed below must also be reported in routine study data submissions in eVelos.** Details of the event must include severity, relationship to study drug, duration, action taken, and outcome as shown on the eCRF in eVelos. All AEs must be followed to resolution or stabilization regardless of relationship to study drug.

All AEs that are considered related to study regimen must be followed to resolution or stabilization if improvement is not expected.

AEs must be reported from the date the subject signs consent through 30 days post-last dose of study treatment or initiation of a new anticancer therapy, whichever occurs first. If a subject is enrolled but discontinues study prior to receiving any study drug, only SAEs that are considered related to study procedures must be reported through the end-of-study visit. AEs that completely resolve and then recur should be recorded as a new AE. For subjects who complete the end of study visit less than 30 days following their last dose of study drug, a follow up of ongoing AEs should be attempted by telephone, and documented in the subject's source. AEs continuing at 30 days post-last dose should have a comment in the source by the treating investigator that the event has stabilized or is not expected to improve. SAEs continuing at 30 days post-last dose should be followed until resolution or stabilization.

The treating investigator is responsible for evaluating all AEs for relationship to study drug and for seriousness, obtaining supporting documents, and determining that documentation of the event is adequate. Adverse events will be assigned a severity grade using the NCI-CTCAE grading scale v4.0. The

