### **Definitions**

#### **Adverse Events of Special Interest**

Adverse events of special interest are events that Janssen Scientific Affairs, LLC is actively monitoring as a result of a previously identified signal (even if non-serious). These adverse events are:

- Infusion reactions:  $\geq$  Grade 3
- Infections:  $\geq$  Grade 4
- Cytopenias:  $\geq$  Grade 4

- HBV reactivation
- Other malignancies

Any adverse event of special Interest that is to be reported to Janssen should be recorded on a Serious Adverse Event Report Form and be reported to Janssen within 24 hours of knowledge of the event.

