### **8.3.4 Pregnancy Reporting**

Pregnancy of a female subject or the female partner of a male subject occurring while the subject is on treatment or within 4 weeks after the subject's last dose of study drug are considered expedited reportable events. Study drugs—lenalidomide, dexamethasone, carfilzomib, and daratumumab—are to be discontinued immediately. The pregnancy must be reported within 24 hours of the treating investigator's knowledge of the pregnancy by phone and facsimile using the SAE form to the University of Chicago CRA either by fax or by email. The treating investigator must inform the University of Chicago in writing by email or facsimile of any pregnancy within 24 hours / 1 business day at the latest on the following workday of being aware of the event. The University of Chicago must report pregnancy as an SAE directly to Amgen, Janssen, and Celgene using expedited reporting procedures listed in Section 8.3.3 and 8.3.3.2.

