21. Peripheral blood and bone marrow aspirate samples collected at screening, end of cycle 8, time of response (to confirm complete response), end-of-treatment visit, and yearly after end of treatment for up to 2 years. Buccal mucosa swab will be collected at screening only.
22. AEs will be collected from the time of signing informed consent. 30 days following the last dose of D-KRD, patients will be considered to be off-study so no toxicities will be recorded following this period. All concomitant medications must be recorded on the concomitant medications case report form from 21 days before Day 1 through 30 days following the last dose of study drugs.
23. Assessment for disease progression in subjects who did not progress during treatment. At least every 3 months (+/- 30 days) for 5 years from safety follow-up visit (which must be 28days (+/- 3 days) post-last study treatment).
24. Lenalidomide must be prescribed through and in compliance with the Revlimid REMS® program of Celgene Corporation. Prescriptions must be filled within 7 days. Consideration should be given to prescribing lenalidomide 5 to 7 days in advance of Day 1 of each cycle to allow time for required patient and prescriber surveys, and drug shipment to patient. Any unused Revlimid® (lenalidomide) should be returned to the patient for disposition in accordance with the Revlimid REMS® program.
25. Cycles 1-8: Days 1, 2, 8, 9, 15 & 16. Cycles 9-24 Days 1, 2, 15 and 16.
26. Daily on Days 1-21 followed by a 7-day rest period every 28 days. On day coinciding with carfilzomib administration, lenalidomide should be taken at least 4 hours after the carfilzomib dose and may be self-administered at home by the subject. On days that carfilzomib is not administered, lenalidomide should be taken at approximately the same time each day.

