27. Days 1, 8, 15 and 22. Dexamethasone is given between 30 minutes and 4 hours before carfilzomib on days they coincide. Dexamethasone will be dosed at 40 mg PO per week during Cycles 1-4 and 20 mg PO per week during Cycles 5-24. Cycles 9-24 represent the D-KRD Maintenance Phase of therapy and the dose of dexamethasone will remain 20 mg on days 1, 8, 15 and 22. For weeks of daratumumab injection, dexamethasone dose is split into two doses: half the dose prior to daratumumab infusion and half the dose the day after. Split weekly dosing for all other days (e.g. 10 mg on Day 1 and 10 mg on Day 2, etc.) is permitted with approval from Lead Principal Investigator. Dexamethasone given on days without carfilzomib (on Days 22 and 23 of Cycles 1-8) may be self-administered by the subject on an outpatient basis. If Day 2 of carfilzomib dosing is delayed (i.e., Day 2, 9, 16) 4 mg of dexamethasone premedication is required to be used prior to second treatment. Missed doses will not be replaced during a cycle. Missed doses of dexamethasone will not be made up. Single-agent lenalidomide maintenance therapy, is recommended using last tolerated dose of lenalidomide for 21 days in 28 day cycles after D-KRD protocol treatment (Cycles 1-24) is completed.
28. Patients will be followed for survival and development of any new cancers, at least every 3 months. Reports of any death should include date of death and specific cause (disease under study or specify other cause).
29. Evaluations at the end of Cycle 8 may be done on Day 1 of the next Cycle 9.

30. Plasmacytoma evaluation is required at screening only and may be completed as physical exam or imaging if indicated and at the treating investigator's discretion. After screening, plasmacytoma evaluation is required only for patients who have no other measurable disease and/or at investigator's discretion.

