31. One bone marrow sample for central Minimal Residual Disease (MRD) analysis by NGS at Adaptive Biotechnologies will be collected from all subjects: 1) screening (sample is required for calibration of MRD by gene sequencing. In the event that a superfluous bone marrow aspirate –BMA- sample from screening was not available, slides of BMA smear or clot from a time prior to enrollment can be used), 2) end of cycle 8, 3) end of cycle 24 (EOT), 4) 1 and 2 years after EOT for all subjects; 5) any time that a bone marrow is performed as SOC to assess CR response. If CR is suspected after cycle 8, the bone marrow biopsy/aspirate must be performed at the end of Cycle 12. For any bone marrow collected after Cycle 8 or Cycle 24, the visit may be done on Day 22-28 of that cycle.
32. A CT-PET will be performed to confirm MRD-negative disease per Standard of Care, at every time-point when MRD is checked (+/- 2 weeks). A bone marrow done as SOC 1 and 2 years after the EOT BM will be tested for MRD and a CT-PET done to confirm MRD-negative disease (+/- 2 weeks).
33. Local testing for hepatitis B surface antigen (HBsAg), hepatitis B surface antibody (Anti-HBs), and hepatitis B core antibody (Anti-HBc). HBV serology is not required at Screening if this was performed as part of standard of care within 3 months prior to first dose.
34. For subjects with serologic evidence of resolved HBV infection (i.e., positive Anti-HBs or positive Anti-HBc) at Screening, HBV DNA testing by PCR must be performed locally.
35. Q12W for up to 6 months after the last dose of study treatment.
36. If administered by subcutaneous (SC) injection, daratumumab will be provided as a fixed-dose of 1800 mg and 30,000 units hyaluronidase per 15 mL (120 mg and 2,000 units/mL) for all cycles. All subjects receiving daratumumab subcutaneous injection will be observed for at least 6 hours after the end of the SC injection during Cycle 1 Day 1 and, if deemed necessary by the treating investigator, after subsequent injections.
37. No provider patient visits will be held on Cycle 1, Day 22.

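### Appendix 8 footnote 22 stops toxicity recording 30 days after the last D-KRd dose, contradicting the protocol's other safety-reporting windows and its own later surveillance

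*Protocol*

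**What the plan says.** Footnote 22 of Appendix 8 starts AE collection at consent and then closes it: "30 days following the last dose of D-KRD, patients will be considered to be off-study so no toxicities will be recorded following this period".

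Other parts of the protocol set different windows or continue surveillance past that point:

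- Section 8.2 reports AEs "through 30 days post-last dose of study treatment or initiation of a new anticancer therapy", whichever is first. Section 6.1.3 records AEs to 30 days after the last treatment and follows related SAEs to resolution.
- Management of Safety Data, in the Janssen part of Section 8.3, wants all AEs for daratumumab, regardless of causality, up to the subject's last study-related procedure, which may be a follow-up safety contact. The same paragraph ends SAE reporting 30 days after the last dose.
- Adverse Events of Special Interest, also in the Janssen part, lists "HBV reactivation" and other malignancies. These go on an SAE form within 24 hours of knowledge, with no end date.
- Appendix 8 schedules HBV DNA testing "Q12W for up to 6 months after the last dose of study treatment" (printed footnote 35).
- Printed footnote 28 says: "Patients will be followed for survival and development of any new cancers, at least every 3 months". Footnote 23 follows non-progressors for progression for 5 years.
- Section 4.1 has patients who complete 24 cycles go on to single-agent lenalidomide: "This regimen will continue until there is progression of the disease or the toxicities require discontinuation of the drug". Printed footnote 27 only recommends that maintenance, and places it after protocol treatment has been completed.

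**The concern.** Footnote 22 is an instruction not to record, rather than a detail left open. It sits in the schedule that site staff work from day to day. If it is followed, a site may carry out surveillance the protocol requires while being told that the findings are no longer collected. If the Janssen text is followed, the same event is reportable within 24 hours. Two sites acting in good faith would then hold different safety data.

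Safety and tolerability is a secondary endpoint (Section 3.2), and Section 10.2.3 compares toxicity with historical KRd+ASCT data. A recording window that varies by site, and is short for late-onset events, would affect both.

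**Working it through.** The plan gives no figure to reproduce. The check sets the windows side by side and then places the scheduled surveillance on a day count from the last dose.

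| Place | Covers | Clock starts | Clock ends |
|---|---|---|---|
| Appendix 8, footnote 22 | Toxicities | Last D-KRd dose | 30 days, then off study |
| Section 6.1.3 | AEs | Last treatment | 30 days |
| Section 8.2 | AEs | Last dose of study treatment | 30 days or new anticancer therapy |
| Section 8.3, Management of Safety Data | All AEs | Consent | Last study-related procedure |
| Same paragraph | SAEs | Last dose of study drug | 30 days |
| Section 8.3, Adverse Events of Special Interest | HBV reactivation, other malignancies and others | Knowledge of the event | None stated |

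Three conflicts follow. Footnote 22 and Management of Safety Data give different end points for AEs. Management of Safety Data itself gives the more serious category the shorter window. The 30-day clocks start from three differently worded events.

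**HBV DNA testing** (at-risk subjects only, Section 6.2.6)

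- The End of Treatment test is nominally on day 28 (Section 6.1.3, ±7 days). Since 28 ≤ 30, it is inside the window.
- Counting 12-week intervals from the last dose: 12 × 7 = day 84, and 2 × 84 = day 168. Both are after day 30. A third at 3 × 84 = day 252 is past 6 months (about 183 days).
- So 1 of 3 post-treatment tests falls inside the window and 2 of 3 fall after it. The window covers 30/183 = 16% of the surveillance period, leaving 183 − 30 = 153 days.
- If the interval is counted from the day-28 test instead, the next is 28 + 84 = day 112, and the one after, day 196, is past 6 months. The number of later tests changes, but none falls before day 30.

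**New-cancer contacts**

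- Section 4.1.4 counts 3-monthly contacts from the safety follow-up visit (about day 28): 28 + 91 = day 119. With the 30-day tolerance of Section 6.6.1, the earliest is 119 − 30 = day 89, which is after day 30.
- None of about 8 contacts (2 years × 4) or about 20 (5 years × 4) falls inside the window. Both lengths are shown because the protocol gives 2 years in some places and 5 in others.

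**Lenalidomide after Cycle 24**

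- Let L be the days from the last D-KRd dose to the last maintenance dose. Footnote 22 covers 30 days. If maintenance is study treatment, Section 8.2 covers L + 30. The two differ by (L + 30) − 30 = L days, so each 28-day maintenance cycle adds 28 days.
- If maintenance is not study treatment, the two windows agree. The protocol does not define the term, and Section 4.1 and footnote 27 point in opposite directions.

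**The case against.** The strongest counter-argument is that a reporting route exists. Management of Safety Data reaches to the last study-related procedure, the special-interest list has no end date, and the Janssen reporting procedures require all AEs after daratumumab exposure to be entered in the CRF. New-cancer evaluation has its own row in the long-term follow-up column. HBV testing is limited to at-risk subjects, and HBsAg-positive or PCR-positive patients are excluded at entry. All of this stands. It means the defect is a contradiction rather than a missing route. It does not cure the contradiction, because footnote 22 still tells sites the opposite. The follow-up of SAEs still ongoing at day 30 (Section 8.2) does not help with events that begin later.

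Four stronger readings are tempting but not supported.

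- A reader might infer that late reactivations and cancers simply go unrecorded. That follows only if footnote 22 is read alone.
- A reader might infer that every post-treatment HBV test misses the window. The End of Treatment test nominally falls inside it.
- A reader might infer that all maintenance-phase toxicity is lost. That holds on the footnote 22 clock only. Section 8.2 may cover it, and the Celgene SAE rule states no post-dose cut-off. The safety endpoint is also worded for the D-KRd combination, so it is arguable whether single-agent lenalidomide toxicity belongs to it.
- A reader might set the four-week pregnancy clause of Section 8.3.4 (after the subject's "last dose of study drug are considered expedited reportable events") against contraception "during therapy, during dose interruptions and for 90 days following the last dose of drug" and infer a reporting gap. The Amgen and Janssen pregnancy rules set no four-week limit, and Appendix 7 uses 28 days for lenalidomide contraception.

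**Conclusion.** The contradiction is real, and the point holds in a limited form. Footnote 22 conflicts with the Janssen AE and special-interest rules and with the follow-up in footnotes 23 and 28. It also starts its clock at a different point from Sections 6.1.3 and 8.2. In at-risk subjects, two of three post-treatment HBV DNA tests fall after the cut-off, as do all scheduled new-cancer contacts. Events found there would be recorded inconsistently, or lost at sites that follow footnote 22.

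Any resulting bias in late safety counts would be downward. Its size cannot be computed, because the documents give neither the number of at-risk subjects nor an expected rate of late events. Special-interest counts are a company reporting duty rather than a listed endpoint, so the effect runs through the general safety endpoint and the historical toxicity comparison.

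The day counts assume 12-week intervals from the last dose, 6 months of about 183 days, 3 months of about 91 days and a safety visit near day 28. The Cycle 8 primary endpoint, its test and the sample size are untouched. This should be corrected, but it does not put the trial's main conclusion at risk.

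**What to change.** By amendment:

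1. Delete from footnote 22 the statement that patients are off study and that toxicities are no longer recorded.
2. Bring footnote 22, Sections 6.1.3 and 8.2 and Management of Safety Data to one defined last dose of study treatment. State whether lenalidomide after Cycle 24 counts as study treatment, reconciling Section 4.1 with footnote 27. Resolve the AE and SAE windows in Management of Safety Data so that SAEs do not have the shorter one.
3. State that three kinds of event are recorded and reported after day 30: HBV reactivation found through the 6-month testing period; new malignancies found in follow-up; and treatment-related SAEs, including those on maintenance lenalidomide if it is study treatment.

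The cost is amendment wording and a few CRF entries at tests and contacts already scheduled. No new procedure or visit is needed.

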### **6.3.2 Lenalidomide Administration**

US: Lenalidomide will be prescribed and obtained commercially in accordance with the Revlimid REMS® program of Celgene Corporation. Per standard Revlimid REMS® requirements, all investigators who prescribe lenalidomide for research subjects enrolled into this trial must be registered and must comply with all requirements of the Revlimid REMS® program. Prescriptions must be filled within 7 days. Only enough lenalidomide for one cycle of therapy will be supplied to the patient each cycle. Unused lenalidomide will be counted and documented by each site. Unused lenalidomide will be returned to Celgene by the site using instructions provided by Celgene.

Subjects will receive lenalidomide as follows in 28-day cycles:

- Cycles 1-24: 25 mg (or best tolerated dose) PO Days 1-21

Lenalidomide should be taken each evening at approximately the same time. Lenalidomide is taken with water on a full or empty stomach. Subjects should not break, chew or open capsules. If possible, late doses of lenalidomide should be taken on the assigned day but should not be made up the next day. Vomited doses will not be made up. Subjects should be instructed to never take lenalidomide past Day 21 of each cycle.

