#### **Pregnancy Reporting by Lead Principal Investigator to Celgene**

For lenalidomide pregnancies and suspected pregnancies (including a positive pregnancy test regardless of age or disease state) of a female subject occurring while the subject is on lenalidomide, or within 28 days of the subject's last dose of lenalidomide, are considered immediately reportable events. Lenalidomide is to be discontinued immediately and the subject instructed to return any unused portion of the lenalidomide to the investigator. The pregnancy, suspected pregnancy, or positive pregnancy test must be reported to the Lead Principal Investigator who will inform Celgene immediately using the Pregnancy Reporting Form provided by Celgene or an approved equivalent form. The exposure of any pregnant female (e.g., caregiver or pharmacist) to lenalidomide is also an immediately reportable event.

The female subject should be referred to an obstetrician-gynecologist, preferably one experienced in reproductive toxicity for further evaluation and counseling.

The Lead Principal Investigator will follow the female subject until completion of the pregnancy, and must notify Celgene immediately about the outcome of the pregnancy (either normal or abnormal outcome).

If the outcome of the pregnancy was abnormal (e.g., spontaneous or therapeutic abortion), the Investigator should report the abnormal outcome as an AE. If the abnormal outcome meets any of the serious criteria, it must be reported as an SAE within 24 hours of the investigator's knowledge of the event using the SAE Report Form, or MedWatch Form.

All neonatal deaths that occur within 28 days of birth should be reported, without regard to causality, as SAEs. In addition, any infant death after 28 days that the Investigator suspects is related to the in utero exposure to the lenalidomide should also be reported within 24 hours of the investigator's knowledge of the event using the SAE Report Form, or approved equivalent form.

If a female partner of a male subject taking investigational product becomes pregnant, the male subject taking IP should notify the investigator, and the pregnant female partner should be advised to call their healthcare provider immediately.

If a pregnancy related event is reported in a female partner of a male subject, the investigator should ask if the female partner is willing to share information with Celgene Drug Safety and allow the pregnancy related event to be followed up to completion.

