### **9.2.2 Supply**

Lenalidomide (Revlimid) will come from commercially-available supply. Lenalidomide will be provided in accordance with Celgene Corporation's Revlimid REMS® program. Per standard Revlimid REMS® program requirements, all physicians who prescribe lenalidomide for research subjects enrolled into this

trial, and all research subjects enrolled into this trial, must be registered in, and must comply with, all requirements of the Revlimid REMS® program.

Lenalidomide will be shipped to the subjects' homes directly. If any unused drug is returned to the site by the subject it should be destroyed according to the local pharmacy's destruction policy

Further information about the Revlimid REMS® program is available at [www.celgeneriskmanagement.com](http://www.celgeneriskmanagement.com).

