### **9.2.4 Accountability**

Bottles of lenalidomide will contain a sufficient number of capsules to last for one cycle of dosing. Sites will be required to record and document subject compliance regarding lenalidomide dosing.

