### **1.5.3. Additional Precautions**

- Subjects should be instructed to never give lenalidomide to another person.
- Subjects should be instructed to return any unused capsules to the study doctor.
- Subjects should not donate blood while receiving lenalidomide, during dose interruptions and for at least 28 days after the last dose of lenalidomide.
- No more than a 28-day lenalidomide supply may be dispensed with each cycle of lenalidomide.

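### The protocol contradicts itself on unused lenalidomide: Appendix 8 footnote 24 sends it back to the patient against every other instruction, and sections 6.3.2 and 9.2.2 give different end points for drug the site holds.

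*Protocol*

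**What the plan says.** Five places in the protocol say where unused lenalidomide goes.

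- **Appendix 8, footnote 24**, attached to the row on REMS registration and prescribing: "Any unused Revlimid® (lenalidomide) should be returned to the patient for disposition in accordance with the Revlimid REMS® program".
- **Appendix 7, section 1.5.3**, part of a plan that covers every subject on lenalidomide: "Subjects should be instructed to return any unused capsules to the study doctor".
- **Section 8.3.4, pregnancy reporting to Celgene**: when a pregnancy occurs or is suspected, the drug is stopped and "the subject instructed to return any unused portion of the lenalidomide to the investigator".
- **Section 6.3.2**: "Unused lenalidomide will be counted and documented by each site", followed by "Unused lenalidomide will be returned to Celgene by the site using instructions provided by Celgene".
- **Section 9.2.2**: "If any unused drug is returned to the site by the subject it should be destroyed according to the local pharmacy's destruction policy".

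Section 9.2.4 adds a related duty: "Sites will be required to record and document subject compliance regarding lenalidomide dosing".

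**The concern.** Site staff work from the Schedule of Events, and section 6 points readers to it. Its footnote 24 moves capsules towards the patient, while every other instruction moves them away. The reference to the REMS program makes the footnote look authoritative.

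Two things are at stake. The first is fetal-exposure control: Appendix 7 section 1.1 does not exclude a teratogenic effect in humans, and the pregnancy-reporting section treats exposure of any pregnant female, caregivers included, as immediately reportable. Leftover capsules in the home work against that plan. The second is drug accountability. Sections 6.3.2 and 9.2.4 ask for a count and a compliance record, and sites that follow different instructions may keep records that do not match. Even a site that ignores footnote 24 has no single answer on whether returned drug goes to Celgene or is destroyed locally.

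**Working it through.** No calculation applies. The check is to set the instructions side by side and ask which can be followed together.

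| Place in protocol | Step covered | Instruction |
|---|---|---|
| Appendix 7, 1.5.3 | subject to site | to the study doctor |
| 8.3.4, Celgene pregnancy reporting | subject to site | to the investigator |
| 6.3.2, first sentence on unused drug | at the site | count and document |
| 6.3.2, next sentence | site to end point | to Celgene |
| 9.2.2 | site to end point | local destruction, if the subject returns drug |
| Appendix 8, footnote 24 | towards the patient | to the patient, for disposition under REMS |

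**Step 1: which instructions agree.** Appendix 7, the pregnancy-reporting section and the count in section 6.3.2 form a consistent first stage: the subject hands capsules in and the site counts them. Either end point could follow, so these do not conflict with one another, with the return to Celgene, or with local destruction.

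**Step 2: first conflict.** Footnote 24 runs the other way. Section 9.2.2 says lenalidomide is shipped straight to subjects' homes, so a site would normally hold unused capsules only because the subject brought them back. Read literally, footnote 24 gives the subject what Appendix 7 has just had the subject hand in. It cannot be combined with return to Celgene or with destruction at the site.

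**Step 3: second conflict.** Sections 6.3.2 and 9.2.2 both address drug that has reached the site. One ships it to Celgene and the other destroys it locally. Section 9.2.2 is conditional on the subject returning drug, but that is the situation section 6.3.2 also covers, so the condition does not separate them.

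**Step 4: are the conflicts independent?** Footnote 24 may be a slip, with *to the patient* written for *by the patient*. Correcting that word would remove the first conflict and leave the second.

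**Step 5: what the analysis uses.** Section 3.2 measures safety and tolerability by frequencies of adverse events, serious adverse events and events leading to discontinuation. Section 10.2.3 tabulates toxicity grades. The primary analysis in section 10.2.2 uses sCR and MRD status. None of these takes capsule counts as an input.

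**The case against.** The strongest reply is that this is one misworded footnote with safeguards around it. Footnote 24 does not simply hand capsules back; it ties disposition to the REMS program, whose requirements are not in the documents. Appendix 7 already forbids giving the drug to others, limits each supply to 28 days and requires counselling at each dispensing. These safeguards reduce the risk and belong in the assessment. They do not remove the contradiction, because Appendix 7 itself has capsules returned to the study doctor.

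A reader might infer more than the text supports, in four ways.

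- **That all the routes are mutually incompatible.** They are not. Return to the doctor is the first leg of either end point, so there are two conflicts.
- **That the required capsule counts must fail.** A site could count capsules before handing them back, and section 9.2.4 requires a compliance record rather than retention of capsules. The count is put at risk and no more.
- **That tolerability data become unreliable.** No stated tolerability endpoint uses capsule counts.
- **That leftovers of a superseded strength are routine.** The documents give no frequency of holds or reductions. Several holds resume at full dose, for example after a first ANC fall (Table 6-7) or tumor lysis (Table 6-8).

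**Conclusion.** The point holds as an internal contradiction in drug-handling instructions. Footnote 24 conflicts with Appendix 7 section 1.5.3, the pregnancy-reporting section and sections 6.3.2 and 9.2.2. Separately, sections 6.3.2 and 9.2.2 disagree on the end point for drug the site holds. All are in the current text.

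The consequence is limited to handling: a site that takes footnote 24 literally could leave capsules with patients, against the pregnancy prevention plan, and could weaken the count and compliance record. This assumes that some sites act on the footnote as worded and that the REMS reference does not redirect the drug elsewhere; the documents settle neither. No rate of leftover capsules can be derived. Sample size and the primary analysis are untouched. It merits correction because the drug is under a pregnancy prevention plan and the correction is cheap.

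**What to change.** Correct the last sentence of Appendix 8 footnote 24, and reconcile it with Appendix 7 section 1.5.3, the Celgene pregnancy-reporting section, section 6.3.2 and section 9.2.2. State one chain once and refer to it from the other places: who receives unused capsules, who counts and documents them, and whether they are then shipped or destroyed. The sponsor must choose the end point; this review does not.

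The cost is wording in the next amendment, since sections 6.3.2 and 9.2.4 already require the count and the compliance record. The reconciliation needs no new rule on when the count takes place. Such a rule might not be free, because the drug is shipped to subjects' homes and footnote 24 suggests prescribing 5 to 7 days before Day 1.
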